The primary outcome is tobacco use (Yes/No, defined as active use in the last 7 days) and the secondary outcome is the presence of surgical complications (classified into respiratory, cardiovascular, wound complications, and mortality).

The specific objectives are the following:

To compare the effectiveness of the intervention in terms of abstinence, patient evolution, motivation and the attempts to quit smoking between the patients in the IG and the CG undergoing one of the two types of surgery.To compare the length of hospital stay (in days) and the number of re-admissions between the IG and the CG according to type of surgery.To compare surgical and post-surgical complications and mortality rates between the IG and the CG up to 90 days post-surgery.To assess whether the intervention can be implemented in the health system in Spain.

These objectives will be analyzed by comparing the results obtained in the IG and CG at the following time points: before surgery (at the beginning of the study), on the day of surgery, and at 1, 3, 6 and 12 months post-surgery (Table 1).

**Table 1 t0001:** Plans for assessment and collection of different variables in surgical patients who participate in the RCT at the Vall d´Hebron University Hospital, Barcelona (N=232)

*Variables*	*Baseline*	*Day of* *surgery*	*1 month* *post-surgery*	*3 months* *post-surgery*	*6 months* *post-surgery*	*12 months* *post-surgery*	*Re-admission*
Sociodemographic data	x						
Specialty	x						
Type of SI	x						
Smoker (yes/no)	x	x	x				
Type of consumption	x						
Amount of consumption	x	x	x (if s)	x (if s)	x (if s)	x (if s)	
Fagerström test	x		x (if s)	x (if s)	x (if s)	x (if s)	
Stages of change	x		x (if s)	x (if s)	x (if s)	x (if s)	
Richmond test	x		x (if s)	x (if s)	x (if s)	x (if s)	
Previous abstinence	x						
Previous drugs	x						
Living with smoker	x						
Comorbidities	x						
General self-efficacy scale	x						
CO-oximetry		x					
ASA PS classification		x					
ATB prophylaxis		x					
Duration of surgery		x					
Blood transfusion		x					
SatO2 at start of surgery		x					
Complications of surgery		x					
Complications at time of recovery room care discharge after surgery		x					
Attempts to quit			x (if s)	x (if s)	x (if s)	x (if s)	
Decrease in consumption			x (if s)	x (if s)	x (if s)	x (if s)	
Pharmacological treatment			x	x	x	x	
Is lack of NRT funding a problem?			x	x	x	x	
Readmission (yes/no)							x
Reason for readmission							x
SSI							x

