### Outcome variables

The main outcome variable will be tobacco use (Yes/No, defined as active use in the last 7 days)^25^ at the various time points. Abstinence validation will be performed with CO-oximetry on the day of surgery and at 12 months for subjects who declare themselves abstinent (patients with CO >6 ppm will be considered as active smokers)^26^. At the other time points (start of the study, and at 1, 3, 6 and 12 months) abstinence will be self-reported by the patient. The following secondary variables will be recorded at each assessment: 1) type of tobacco product (cigarettes, rolling tobacco, cigars, etc.); 2) pattern of consumption of each type of tobacco product (daily or occasional, and daily/weekly amount); and 3) level of nicotine dependence, using the Fagerström test (low 0–3, medium 4–6, and high 7–10)^27^. Other variables that will be assessed include motivation and self-efficacy, willingness to quit smoking according to the Prochaska and Di Clemente model^28^, level of motivation using the Richmond test^29^; and the General self-efficacy scale (based on Bandura’s social cognitive theory)^30^.

Another outcome variable will be surgical complications classified into the following groups and assessed on the day of surgery, on discharge from recovery-room care, hospital discharge, and up to 90 days post-surgery: 1) respiratory complications (bronchospasm, respiratory failure requiring oxygen and active treatment, respiratory superinfection requiring antimicrobial treatment, pleural effusion, other); 2) cardiovascular complications (deep venous and pulmonary thromboembolic disease, hypertensive crises, angina, new onset arrhythmias/blockages, acute myocardial infarction, heart failure, other); 3) postoperative complications of the surgical wound (dehiscence, fistula or infection of the internal or deep wound, seroma, wall abscess or fistula of the external wound with antimicrobial treatment and positive cultures, other); and 4) mortality (during hospitalization and within 90 days of surgery). All complications after the day of surgery will be recorded taking into account data from the patient’s medical history. Variables related to surgery: surgical time, blood transfusions (to be assessed as possible confounding variables for post-surgical complications and mortality). Variables related to hospital care: length of hospital admission (in days); and readmissions required within 12 months of hospital discharge.

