### Independent variables

The main independent variable will be ‘implementation of an intensive pre-surgical intervention to stop smoking’ (Yes/No). In addition, the following data will be recorded:

Sociodemographic variables such as sex, age, marital status, living with a smoker, education level, type of surgery.Comorbidities.Pharmacological treatment: none/NRT according to the recommendations of the different guidelines^15,31^.

The variables to be recorded and the frequency of recording are detailed in Table 1.

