### Procedure

This pragmatic intervention will be carried out at different hospital services and will involve healthcare professionals from different ambits for evaluation. The intervention will begin in the pre-surgical period, at the pre-anesthetic visit, where smokers who meet the inclusion criteria outlined in the protocol will be invited to participate. Those who agree will receive more detailed explanations of the nature of the study and they will be asked to provide written informed consent. An information leaflet (see Supplementary file) will be provided to all patients who agree to take part. Within 24–48 hours they will receive a telephone call during which baseline data will be recorded, and at the end of the interview, patients will be randomly assigned to the IG or the CG. Participants will receive the following, according to their group.

*Intervention group (IG)*

Intensive intervention consisting of two pre-surgical visits starting at least four weeks before surgery (depending on the type of surgery) + an information leaflet (see Supplementary file) + pharmacological therapy (NRT if needed) + four follow-up consultations by telephone, carried out by expert staff trained in intensive smoking interventions (at 1, 3, 6 and 12 months after surgery) with the aim of maintaining abstinence.

*Control group*

A single visit with brief advice to stop smoking and the same information leaflet between three and six weeks before surgery (depending on the type of surgery) provided by healthcare personnel. Follow-up after discharge will be by telephone at 1, 3, 6 and 12 months after discharge, but no more advice will be given.

The intervention procedure is detailed in Figure 1.

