## DISCUSSION

Smoking is a major risk for patients undergoing surgery. Surgical complications are associated with smoking increasing readmission rates, prolonging hospital stays and ultimately increasing healthcare costs.

Smokers scheduled for surgery are at an ideal time to try a quit attempt^32^. Intensive interventions initiated at preoperative visits are known to be effective^17^ and can reduce complications. Despite this evidence, little help in this regard is offered during pre-surgical visits^33^. This study is the first in Spain to evaluate the effectiveness of an intensive pre-surgical intervention comprising psychological and behavioral support, pharmacological therapy, and a one-year follow-up program designed to help patients quit smoking before they undergo surgery.

The sample size and stratification will allow us to perform subgroup analyses, and the one-year follow-up period will enable us to obtain longterm abstinence data comparing CO-oximetry measurements made on the day of surgery and at the end of the study.

The main expected result is the achievement of an abstinence rate that is 15% higher among patients in the IG compared to those in the CG, and, at the same time, a reduction in the risk of complications in the IG. The analyses will also consider sociodemographic variables, comorbidities, type of surgery, and surgical variables such as duration and transfusions required. Other important results for comparison between groups will be motivation, dependence, cessation attempts, and reduction in consumption.

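### Surgical time and transfusions arise after randomisation, so they cannot confound the comparison of arms; adjusting for them could bias the estimated effect on complications and mortality

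*Protocol article*

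**What the plan says.** Under Outcome variables, the protocol article describes the variables related to surgery as "surgical time, blood transfusions (to be assessed as possible confounding variables for post-surgical complications and mortality". The Discussion returns to them: "The analyses will also consider sociodemographic variables, comorbidities, type of surgery, and surgical variables such as duration and transfusions required". Baseline characteristics and intra-operative variables stand there in one list, with no distinction between them.

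The order of events is given elsewhere. Under Procedure, once the baseline telephone interview is complete, "at the end of the interview, patients will be randomly assigned to the IG or the CG". The IG then receives "two pre-surgical visits starting at least four weeks before surgery". Table 1 has rows for "Duration of surgery" and "Blood transfusion", each marked in the day-of-surgery column and in no other.

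The Data analysis section compares complications between IG and CG with hazard ratios from Cox regression. It commits all analyses to intention to treat and names no covariates for these models. Nothing in the article confines surgical time or transfusions to a descriptive, sensitivity or mediation analysis.

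**The concern.** A confounder of a treatment comparison must influence, or share a cause with, the assignment of treatment. Random assignment breaks that link for every variable, and a variable that arises weeks after assignment cannot have influenced it. If surgical time or transfusion differs between arms, the difference is either chance or an effect of the intervention. Testing these variables as confounders and adjusting where they look imbalanced or associated with the outcome would treat a possible effect of the intervention as a nuisance to be removed.

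Two things could go wrong. If stopping smoking shortens operations or reduces transfusion, and this in turn lowers complications, adjustment takes that part out of the estimate. If these variables share unmeasured causes with the complications, such as frailty or a technically difficult operation, or follow from a complication during surgery, conditioning on them can create an association between arm and outcome that assignment did not cause.

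Complications and mortality are the secondary outcome, and the Discussion names a lower complication risk as an expected result, so the estimate will be read closely.

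**Working it through.** The plan gives no figure on this point, so there is none to reproduce. The check has two parts: the order of events, then an illustration of size with assumed effects.

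**1. Order of events**

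| Step | When | Source |
|---|---|---|
| Randomisation | End of the baseline call, before surgery | Procedure |
| Intervention starts | At least four weeks before surgery | Procedure |
| Purpose before surgery | To have the patient stop smoking by then | Components of the intensive intervention |
| Surgical time and transfusion recorded | Day of surgery only | Table 1 |
| Complications assessed | Day of surgery up to 90 days | Outcome variables |

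Both variables come after assignment and after the pre-surgical part of the intervention. With respect to arm, each is either unaffected, a mediator, or affected by arm and also linked to the outcome through a shared cause or an early complication. None of these makes it a confounder. Complications are counted from the same day, so a transfusion or a longer operation may itself result from an outcome event.

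**2. Size if part of the effect is mediated**

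Assumptions: true total hazard ratio 0.60, and a fraction f of the log effect running through the two variables. Neither comes from the documents. As a rough rule that ignores non-collapsibility of the hazard ratio, the adjusted hazard ratio is 0.60^(1 − f):

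- f = 0: 0.60
- f = 0.2: 0.60^0.8 = 0.66
- f = 0.3: 0.60^0.7 = 0.70
- f = 0.5: 0.60^0.5 = 0.77

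**3. Simulation**

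A logistic model was simulated with 400,000 patients allocated 1:1 and one post-randomisation variable M. All effects are assumed: intercept −1.5 throughout. In the mediation rows, M changes the log odds by 0.5 per unit; the direct arm effect on the log odds is −0.5 in the first three rows and zero in the fourth. In the last row, M has no effect on the outcome, arm shifts M by −0.5, and an unmeasured cause acts on both M and the outcome with coefficient 1.

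| Assumed case | Odds ratio for arm, unadjusted | Adjusted for M |
|---|---|---|
| Arm does not change M | 0.61 | 0.60 |
| Arm lowers M by 0.2 SD | 0.56 | 0.60 |
| Arm lowers M by 0.5 SD | 0.49 | 0.62 |
| Effect wholly through M | 0.79 | 1.01 |
| No true effect; arm changes M; shared unmeasured cause | 1.01 | 1.28 |

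The unadjusted column is the total effect of assignment. Adjustment leaves it almost unchanged in the first row, moves it toward 1 in the next two, removes it in the fourth, and produces an apparent harm in the last.

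**The case against.** **Adjustment is signalled, not fixed.** The text speaks of assessing possible confounders, the Discussion says only that the analyses will consider these variables, and Data analysis lists no covariates. A reader might infer that the complication models will certainly adjust for them and so will remove part of the effect. The article does not go that far. What it does state is the role these variables are to play, and that role is wrong whatever a fuller document lists.

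**The bias is conditional.** Nothing in the article says the intervention changes surgical time or transfusion. The smoking harms listed in the Introduction include wound problems, infarction, pneumonia and infection, but not operating time or blood loss. Surgeons are blinded, which limits differences in how the operation is carried out. The procedures range from ligament repair to cystectomy, so the type of operation may drive much of the variation in duration. This stands, and the range of possible bias must start at none. Type of surgery, however, is known at baseline and can serve as a case-mix adjustment without the risk.

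**Nicotine replacement therapy (NRT).** The Independent variables section lists "Pharmacological treatment: none/NRT according to the recommendations of the different guidelines". A reader might infer that NRT use, which is part of the IG package, will be adjusted for in the abstinence model. The documents do not support this. The item appears among data to be recorded, the Discussion's list of variables to be considered omits it, and no model is said to include it. No criticism of the primary outcome follows.

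**Conclusion.** The point holds for surgical time and transfusions, and for complications and mortality only. Given the stated order of events, calling them possible confounders of the IG v CG comparison is an error. A model that adjusts for them does not estimate the total intention-to-treat effect.

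Whether the estimate would be materially biased is not known from the documents. The range runs from essentially no change, if the intervention does not affect these variables, to the illustrative 0.66 to 0.77 in place of 0.60. That upper part rests on an assumed hazard ratio and an assumed mediated share of 20% to 50%. A shared unmeasured cause could also distort the estimate when there is no true effect. The primary abstinence outcome and the sample size are not affected.

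**What to change.** Under Outcome variables, delete the confounder role for surgical time and transfusions, and remove "surgical variables such as duration and transfusions required" from the Discussion's list or say there that they are descriptive or exploratory. Under Data analysis, state that the main IG v CG models for complications and mortality adjust only for variables measured before randomisation: for example type of surgery, with age or comorbidities added as the number of events allows. Report surgical time and transfusions by arm, or use them in a separately labelled mediation or exploratory analysis.

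This costs a sentence or two and needs no new data. At the time of the article 25 of 232 participants had been recruited, so a change made at that stage would precede the results.

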### Independent variables

The main independent variable will be ‘implementation of an intensive pre-surgical intervention to stop smoking’ (Yes/No). In addition, the following data will be recorded:

Sociodemographic variables such as sex, age, marital status, living with a smoker, education level, type of surgery.Comorbidities.Pharmacological treatment: none/NRT according to the recommendations of the different guidelines^15,31^.

The variables to be recorded and the frequency of recording are detailed in Table 1.

### Procedure

This pragmatic intervention will be carried out at different hospital services and will involve healthcare professionals from different ambits for evaluation. The intervention will begin in the pre-surgical period, at the pre-anesthetic visit, where smokers who meet the inclusion criteria outlined in the protocol will be invited to participate. Those who agree will receive more detailed explanations of the nature of the study and they will be asked to provide written informed consent. An information leaflet (see Supplementary file) will be provided to all patients who agree to take part. Within 24–48 hours they will receive a telephone call during which baseline data will be recorded, and at the end of the interview, patients will be randomly assigned to the IG or the CG. Participants will receive the following, according to their group.

*Intervention group (IG)*

Intensive intervention consisting of two pre-surgical visits starting at least four weeks before surgery (depending on the type of surgery) + an information leaflet (see Supplementary file) + pharmacological therapy (NRT if needed) + four follow-up consultations by telephone, carried out by expert staff trained in intensive smoking interventions (at 1, 3, 6 and 12 months after surgery) with the aim of maintaining abstinence.

*Control group*

A single visit with brief advice to stop smoking and the same information leaflet between three and six weeks before surgery (depending on the type of surgery) provided by healthcare personnel. Follow-up after discharge will be by telephone at 1, 3, 6 and 12 months after discharge, but no more advice will be given.

The intervention procedure is detailed in Figure 1.

**Figure 1 f0001:**
[figure not shown]
Intervention procedure in the RCT at the Vall d’Hebron University Hospital, Barcelona (N=232)

### Components of the intensive intervention

The intervention is based on the recommendations of smoking cessation treatment guidelines^15,31.^ The intervention aims to ensure that the patient stops smoking before surgery and remains abstinent for as long as possible. It comprises an initial face-to-face visit lasting between 30 to 45 minutes approximately four weeks prior to surgery, and a second telephone visit approximately two weeks prior to surgery. After surgery, patients will be followed up by telephone, with visits after 1, 3, 6 and 12 months. The professionals who will carry out the intervention are experts in the treatment of tobacco addiction and are members of the Preventive Medicine service of the hospital. The components of the various visits are detailed in Table 2.

**Table 2 t0002:** Components of intensive intervention visits in the RCT at the Vall d’Hebron University Hospital, Barcelona (N=232)

*Visits*	*Components*
**First visit** Face-to-face	Assessment of nicotine dependence (Fagerström test). Assessment of stage of change (Prochaska and DiClemente). Assessment of motivation (Richmond test). Assessment of general self-efficacy. Establishment of a plan to quit smoking, emphasizing the benefits of the upcoming surgery. If possible, setting a date to quit, ‘D’ day (try to make it as soon as possible before surgery). Prediction of difficulties that may arise, particularly the first few weeks, including symptoms of nicotine withdrawal syndrome. Recommendation of the use of pharmacological therapy (NRT) if necessary, except when contraindicated. Offer practical advice for problem solving/skills training, learning cognitive and behavioral activities to cope with the desire to smoke. Discussion of difficulties/triggers and how the patient can overcome them (avoiding triggers, changing routines). Description of previous experiences, discussion of what helped and what did not, build on success. Facilitate clinical support throughout the process. Agree on follow-up.
**Second visit** By phone prior to surgery	Assessment of self-reported abstinence. Reinforcement of abstinence before surgery. Assessment of difficulties and problems. Reinforcement of behavioral coping skills and social support. Assessment of adherence to drug treatment and any necessary changes. Recommendation of relapse prevention strategies for patients who remain abstinent. Offer of congratulations emphasizing the benefits of upcoming surgery. Arrangement of follow-up.
**Follow-up visits** By phone after surgery	Assessment of self-reported abstinence. Assessment of treatment adherence and difficulties in following it. Reinforcement of behavioral strategies to cope with smoking urges. Relapse prevention. Recording data on tobacco use and variables if the patient continues to smoke. Measurement of CO-oximetry at the end of the study. Prompt notification of patients who do not attend, so as to try to arrange visits as soon as possible.

### Data collection

Four instruments have been created to record the variables to be studied at each assessment, and another one for randomization using the REDCap application. All the study researchers will be assigned a personal username and password that they will use to access the data and will only be able to access the instruments for which they have authorization. Patients will be informed about the use of the data and the person responsible for their treatment, as well as their rights of access, rectification, cancellation and opposition. Approximately 48 hours after signing the informed consent, baseline data will be recorded and randomization performed. Once the study has finished, the researchers will no longer have access to the database. The Vall d’Hebron Research Institute (VHIR) will be responsible for properly storing the data until their destruction. The database will not identify any of the participants since it will contain only individual encrypted codes. The intervention and data collection procedures using the REDCap application will be previously tested to assess their suitability, if necessary.

### Data analysis

The implementation of the intervention will be evaluated with data on fidelity, dose and scope with respect to the protocol (time spent on visits, use of instruments, barriers and problems detected, recruitment of participants, adherence to treatment, satisfaction). This stage will be carried out prior to the analysis of the results of the RCT. The efficacy of the intervention in terms of abstinence and post-surgical complications will be evaluated by comparing IG and CG. The data will be analyzed separately in the two surgery groups (orthopedic with implants and general/urological). Using the data obtained at the beginning of the study (i.e. a questionnaire with baseline data on tobacco consumption and sociodemographic variables) and the data from the different assessments over the course of the study, descriptive analyses will be performed and a contingency table with bivariate analysis will be created. Logistic regression will be performed to assess the efficacy of the intervention and the rest of the outcome variables. As part of our secondary analyses, we will explore whether the intervention effect varies across different surgical groups by including an interaction term (type of surgery × intervention) in our regression models. Considering the longitudinal nature of our data, a generalized linear mixed binomial family model to account for the correlation between repeated measurements within individuals will be used to assess the evolution of smoking cessation. Hazard ratios (HRs) of surgical complications in the IG and the CG will be calculated using Cox regression models. The proportional hazards assumption will be evaluated using statistical tests (e.g. Schoenfeld residuals) to ensure the validity of the Cox model. The number of patients needed to be treated to achieve cessation in one patient (NNT, and its 95% confidence interval) will be calculated over the one-year period. The NNT is the inverse of the attributable risk and is useful for conveying the efficacy of the intervention to patients, managers and clinicians. All analyses will be performed on an intention-to-treat basis. The level of statistical significance will be set at α=0.05 and the Bonferroni correction will be considered to adjust for multiple comparisons.

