### Sample size and randomization

Every year, approximately 1800 surgical procedures of these kinds are performed at our hospital, of which approximately 25% are carried out in smokers. The sample size has been calculated assuming four equal groups with an estimated difference of 15 percentage points between the predicted rates of abstinence at twelve months in the IG (20%) and the CG (5%). With an expected loss to follow-up rate of 10%, 232 subjects will be needed (58 per group). The sample size has been calculated using the software STATA (StataCorp. 2023. *Stata Statistical Software: Release 18*. College Station, TX: StataCorp LLC). Patients will be assigned to their group by computer-generated random sequence (Stata *ralloc* function) (1:1 assignment) (REDCap). The study will be conducted in a single-blind manner (blinded for surgeons, collaborating researchers, and outcome analysts). There are no circumstances that would necessitate unblinding.

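### The sample size is stated for four groups and the data are to be analysed separately by surgery group, yet within one surgery group power is only about 64% after the planned loss; only the pooled comparison is adequately powered, and it is not named as primary

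*Protocol article*

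**What the plan says.** The relevant statements are spread over four sections of the protocol article.

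- **Sample size and randomization.** "The sample size has been calculated assuming four equal groups with an estimated difference of 15 percentage points" in twelve-month abstinence, 20% v 5%. The result follows: "With an expected loss to follow-up rate of 10%, 232 subjects will be needed (58 per group"). Allocation is "1:1 assignment". Neither the target power nor the sidedness of the test is given.
- **Data analysis.** "The data will be analyzed separately in the two surgery groups (orthopedic with implants and general/urological"). This sentence carries no label such as secondary or exploratory. The surgery-by-intervention interaction does carry one: it is secondary. On multiplicity, alpha is 0.05 and "the Bonferroni correction will be considered to adjust for multiple comparisons".
- **Outcome variables.** The main outcome, tobacco use in the past seven days, is set "at the various time points". The objectives in the Introduction list five assessments after baseline: day of surgery and 1, 3, 6 and 12 months.
- **Discussion.** "The sample size and stratification will allow us to perform subgroup analyses".

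**The concern.** Taken together, these statements tell the reader that 58 per group is enough to compare intervention and control within each surgery group. If it is not, a true 15-point benefit could easily give a non-significant result in orthopaedic or in general/urological patients, and that result could be misread as no effect in that type of surgery.

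The choice of main test is also open. The text allows a pooled test or two separate ones, at twelve months or at any of five assessments. Unless one test is fixed in advance, a reader of the results cannot tell which comparison the 0.05 level protects.

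**Working it through.** **Inputs.** From Sample size and randomization: p1 = 0.20, p2 = 0.05, difference 0.15, 58 per group, four groups, 10% loss, 1:1 allocation. From Data analysis: alpha 0.05. Assumed, because not stated: a two-sided test, and 80% or 90% as the usual power targets.

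**Formulas (two proportions, pooled variance under the null).** With p̄ = 0.125:

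- √(2p̄(1−p̄)) = √0.21875 = 0.4677
- √(p1(1−p1) + p2(1−p2)) = √(0.1600 + 0.0475) = √0.2075 = 0.4555
- n per group = (1.960 × 0.4677 + z_power × 0.4555)² / 0.15²
- power = Φ[(0.15√n − 1.960 × 0.4677) / 0.4555]

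**Step 1: where 232 could come from.**

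- *One pooled two-arm comparison, 90% power:* (0.9167 + 0.5838)² / 0.0225 = 100.1, so 101 per arm. Then 101/0.9 = 112.2, so 113 per arm and 226 in total, within 3% of 232.
- *Separate test in each surgery group, 80% power:* (0.9167 + 0.3834)² / 0.0225 = 75.1, so 76 per group. Then 76/0.9 = 84.4, so 85 per group and 4 × 85 = 340 in total.
- *Other four-group variants* (one- or two-sided, continuity-corrected, unpooled variance, arcsine): none at 80% power or more gives 58 per group once loss is included. The closest is a one-sided arcsine calculation, at 61 to 62. A one-sided unpooled calculation at 80% gives 58 before loss, but 65 after it, and the article presents 58 as already allowing for loss.

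So 232 is close to what a pooled comparison needs and well short of what separate comparisons need.

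**Step 2: power actually available.** Evaluable per group: 58 × 0.9 = 52.2, taken as 52. Pooled per arm: 2 × 52 = 104.

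| Comparison | n per side | (0.15√n − 0.9167)/0.4555 | Power |
|---|---|---|---|
| One surgery group, after loss | 52 | (1.0817 − 0.9167)/0.4555 = 0.362 | 64.1% |
| One surgery group, no loss | 58 | (1.1424 − 0.9167)/0.4555 = 0.495 | 69.0% |
| All patients, after loss | 104 | (1.5297 − 0.9167)/0.4555 = 1.346 | 91.1% |
| All patients, no loss | 116 | (1.6155 − 0.9167)/0.4555 = 1.534 | 93.8% |

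**Step 3: sensitivity to what is not stated.**

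- If all 58 are kept and the lost 10% count as smokers, the rates become 0.9 × 20% = 18% and 0.9 × 5% = 4.5%. Power is 63.6% in one surgery group and 90.7% pooled.
- A one-sided 0.05 test gives 75% with 52 and 79% with 58 in one surgery group.
- Splitting alpha over the two surgery groups (0.025 each) gives 52.9% in each.
- Pooled, 104 per arm keeps 85.5% with two Bonferroni-adjusted tests and 81.6% with three, but 76.2% with five.

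Power within a surgery group stays below 80% in every row.

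**The case against.** The strongest reply is that the plan already contains the adequate analysis. The sentence before the one on separate analysis says efficacy will be judged by comparing intervention with control. An interaction term can be fitted only in a model that includes all patients. The Discussion states the expected 15-point gain for the intervention group as a whole, and Limitations presents stratification as a guard against selection bias, not as two confirmatory tests. The sample size is tied to twelve months, and change over time is assigned to one mixed binomial model. Details of the Bonferroni correction are commonly left to an analysis plan, which is not shown here.

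Much of this stands. A pooled 12-month test is compatible with the text and adequately sized. It does not remove the problem, because the point rests on what the article asserts: a size stated for four groups, an unqualified separate analysis, and a claim that the size supports subgroup analyses. No later plan can make 58 per group sufficient for a separate test.

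Some stronger readings are tempting but not supported:

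- *That ten main tests are planned.* Two surgery groups by five assessments gives ten as an upper illustration. The article nowhere states a separate test at each assessment in each group, so error rates or power built on ten tests do not describe this plan.
- *That success requires significance in both surgery groups.* No such rule is given.
- *That the interaction test is underpowered for its purpose.* It is stated to be exploratory and secondary, which is appropriate.
- *That 232 patients support only a single comparison.* Up to three adjusted pooled tests would keep at least 80% power.

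**Conclusion.** The concern holds as a mismatch between what the article promises and what its size delivers, combined with an unnamed primary test. A true 20% v 5% difference would be missed within a given surgery group about 36% of the time after the planned loss (31% with no loss), against about 9% in the pooled comparison. It does not show that the trial as a whole is underpowered.

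The figures rest on the article's rates and loss, on a two-sided 0.05 test and, for the pooled result, on the same effect in both surgery groups. A one-sided test, or counting lost patients as smokers, does not change the conclusion.

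**What to change.** 1. In Data analysis, name one primary test: abstinence at 12 months, intervention v control, in all randomised patients, by logistic regression adjusted for surgery type, at two-sided 0.05.
2. Label the estimates within each surgery group and at the other time points as secondary, reported with confidence intervals. Keep the interaction secondary, as it already is.
3. In Sample size and randomization, state the power for what will be tested: about 91% pooled and about 64% within each surgery group, both after 10% loss.
4. In the Discussion, drop the claim that the size supports subgroup analyses, or qualify it by saying that these analyses are supportive and have limited power.

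Adjusting also for baseline Fagerström score is optional and is not needed to correct this defect.

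The cost is wording only, with no extra patients. The downside is that surgery-group results become supportive. If separate confirmatory answers are really wanted, the alternative is about 340 patients for 80% power in each group at 0.05, or 412 with alpha split between the two (103 per group × 4). With 25 recruited when the article was written and accrual described as slow, that looks hard to reach.
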